## Abstract

**Objective:**

COVID-19 has led to significant morbidity and mortality globally. Post-COVID sequelae can persist beyond the acute and subacute phases of infection, often termed post-COVID syndrome (PCS). There is limited evidence on the appropriate rehabilitation for people with PCS. The aim of this study is to evaluate the effect on exercise capacity, symptoms, cognition, anxiety, depression, health-related quality of life, and fatigue of a 4-week, twice-weekly supervised pulmonary telerehabilitation program compared with usual medical care for people with PCS with persistent respiratory symptoms.

**Methods:**

The study will be a multi-site randomized controlled trial with assessor blinding. Participants with confirmed previous COVID-19 infection and persistent respiratory symptoms who attend a post-COVID respiratory clinic will be randomized 1:1 to either an intervention group of 4 weeks, twice-weekly pulmonary telerehabilitation or a control group of usual medical care. Participants in the control group will be invited to cross-over into the intervention group after the week 4 assessment. Primary outcome: exercise capacity measured by the 1-minute sit-to-stand test. Secondary outcomes: 5 repetition sit-to-stand test; Montreal Cognitive Assessment; COVID-19 Yorkshire Rehabilitation Scale; Chronic Obstructive Pulmonary Disease Assessment Test; 36-Item Short-Form Health Survey; Hospital Anxiety and Depression Scale; Fatigue Severity Scale; and the Kessler Psychological Distress Scale. Outcomes will be collected at baseline, after 4-weeks intervention or control period, after intervention in the cross-over group, and at 12-month follow-up.

**Impact:**

Research into effective rehabilitation programs is crucial given the substantial morbidity associated with PCS and the lack of long-term data for COVID-19 recovery. A short-duration pulmonary telerehabilitation program, if effective compared with usual care, could inform practice guidelines and direct future clinical trials for the benefit of individuals with persistent respiratory symptoms post-COVID.

## Introduction

The COVID-19 pandemic has led to significant global morbidity and mortality.^1^ In Australia, there have been more than 11 million recorded COVID-19 infections, with over 19,000 directly attributable deaths.^2^ Persistent symptoms post-COVID, commonly termed post-COVID syndrome (PCS), Long COVID, or post-acute sequelae of COVID, can lead to a considerable negative impact on quality of life. For simplicity, PCS will be the term used throughout this article. Common symptoms of PCS include fatigue, post-exertional malaise, (also termed post-exertional symptom exacerbation), dyspnea, anxiety, depression, cognitive impairment or “brain fog”, and in some instances, autonomic dysfunction, including postural orthostatic tachycardia syndrome.^3^ The World Health Organization (WHO) defines PCS as “the continuation or development of new symptoms 3 months after the initial SARS-CoV-2 infection, with these symptoms lasting for at least 2 months with no other explanation.”^4^ A recent systematic review and meta-analysis (*n* = 735,006) shows that 45% of individuals who survive a COVID-19 infection will have at least 1 unresolved symptom at 126 days (~4 months) post-COVID infection regardless of whether they required hospitalization.^5^

There is a substantial body of evidence showing pulmonary rehabilitation improves exercise tolerance, dyspnea, anxiety, depression, and health-related quality of life (HRQoL) for respiratory conditions^6^ including chronic obstructive pulmonary disease,^7^ bronchiectasis,^8^ interstitial lung disease,^9^ chronic asthma,^10^ and pulmonary hypertension.^11^ Less is known about the effectiveness of PR in people with PCS. The timely advent of telehealth has equipped clinicians with the technology and skills necessary to provide telerehabilitation for populations with chronic respiratory conditions and has been shown to be safe and effective.^12^ However, there is limited robust evidence on the effects of exercise rehabilitation (either delivered face-to-face or via telerehabilitation) for people who have respiratory specific sequalae of PCS, which commonly includes dyspnea, chest pain, and cough^13^ and, in some cases, a dysfunctional pattern of breathing.^14^

Since WHO has urged the prioritization of PCS rehabilitation for those experiencing medium and long-term consequences of COVID infection,^15^ some limited, yet encouraging, evidence has emerged. Multiple reviews have shown that PR reduces post-COVID sequelae such as dyspnea^16–18^; improves HRQoL^18^; increases exercise capacity^16^; and promotes the feasibility of service delivery through existing PR pathways.^16^^,^^19^ However, inclusion of primarily low quality studies is a limitation reported by most reviews. To the best of the authors’ knowledge, there are currently no published randomized controlled trials (RCTs) of supervised pulmonary telerehabilitation for people with respiratory specific symptoms of PCS. The aim of this study is to evaluate the effect of a 4-week, twice weekly supervised pulmonary telerehabilitation program on exercise capacity, symptoms, cognition, anxiety, depression, HRQoL, and fatigue compared with usual medical care for people with predominantly respiratory sequelae of PCS.

## Methods

### Participants

Participants who had a COVID-19 infection, confirmed via a rapid antigen test or polymerase chain reaction test, and who were either hospitalized or managed in the community, and who meet the following criteria will be invited to participate in the study.

Inclusion criteria will be people with respiratory sequelae of PCS attending a post-COVID Respiratory Clinic at 2 metropolitan tertiary hospitals in Sydney, Australia; aged 18 years or above; identified by their treating physician as suitable for rehabilitation; and able to provide informed consent. Exclusion criteria will be people with a severe COVID-19 infection admitted to intensive care unit and who develop post–intensive care unit syndrome (such people usually require rehabilitation and therefore cannot take part in a trial where they may be randomized to a control group); acute symptoms of any illness where exercise is not recommended; medically unstable as diagnosed by their treating physician; pregnant or post-partum women; no access to appropriate technology (eg, internet, computer, or tablet); difficulty understanding English and unable to access an interpreter; or severe cognitive impairment or other comorbidities which would make remote exercise unsafe as assessed by the referring physician.

People who meet the inclusion criteria based on their clinic visit will be invited to participate. If agreeable, they will be provided with a participant information sheet and will be contacted by a member of the research team to answer any questions and to complete an online consent form.

### Study Design

This will be a prospective, multi-site, RCT with assessor blinding, and will follow the Guidelines for Reporting Outcomes in Trial Reports (CONSORT). Participants will be randomized into the intervention group (IG) or the control group using a concealed computer-generated sequence, through a secure data management software, Research Electronic Data Capture (REDCap), with a minimization algorithm, stratifying for age (≤50 or >50 years) and sex (male/female). The study has been approved by the Sydney Local Health District (SLHD) Human Research and Ethics Committee and registered on the Australian and New Zealand Clinical Trials Registry (ACTRN 12622000355774).

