#### Fidelity

To ensure that the intervention is delivered consistent with the protocol in this multi-site (4 sites) study, the chief investigator will regularly log into a telerehabilitation session at each site. Any deviations from the study protocol will be discussed immediately after the session so that the intervention is delivered uniformly at all sites.

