### Sample Size

A total of 42 participants will be required to have an 80% chance of detecting, as significant at the 5% level, a between-group difference of 3.5 repetitions in the 1-minSTST (primary outcome), which is the minimal clinically important difference, using a standard deviation of 4 repetitions.^23^ To account for a 15% dropout, 48 participants will be recruited.

The sample size for the semi-structured interviews will be approximately 15 to 20 participants. Interviews will continue until thematic saturation.

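### Recruiting site is neither a minimisation factor nor a planned covariate in a multi-site trial, and the counts of 2 hospitals and 4 sites are not reconciled

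*Protocol article*

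**What the plan says.** The Study Design section states: "This will be a prospective, multi-site, RCT with assessor blinding". The same paragraph gives the allocation rule, run in REDCap "with a minimization algorithm, stratifying for age (≤50 or >50 years) and sex (male/female"). The Abstract's Methods paragraph says participants "will be randomized 1:1 to either an intervention group of 4 weeks, twice-weekly pulmonary telerehabilitation or a control group of usual medical care". No section names site as an allocation factor.

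Two site counts appear. The Participants section recruits people "attending a post-COVID Respiratory Clinic at 2 metropolitan tertiary hospitals in Sydney, Australia". The Fidelity section says that "in this multi-site (4 sites) study, the chief investigator will regularly log into a telerehabilitation session at each site". No text links the two counts.

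The Statistical Analysis section uses a linear mixed effects model for between-group change at the end of the initial period. Covariates enter only if they differ significantly between groups at baseline. No site term is mentioned.

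**The concern.** The protocol itself treats site as a possible source of variation, because it plans checks to keep delivery uniform across sites. Suitability for rehabilitation is judged by each participant's treating physician, and the comparator is usual medical care, for which no standardisation across clinics is described. Case mix, or the course of recovery under usual care, could therefore differ between recruiting clinics.

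If allocation ignores site, chance can leave one clinic mostly in one arm. A site term in the model would then recover the comparison at some cost in precision. Without that term, site differences add noise to the arm difference. Significance-triggered adjustment is a weak safeguard, since a sizeable site imbalance among 48 people can easily miss the 5% level. An analysis plan that is not shown could add a site term, but it cannot change how participants are allocated.

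**Working it through.** **Inputs from the protocol article.** Minimisation on age and sex (Study Design); 1:1 allocation (Abstract); 48 recruited, 42 evaluable, "80% chance of detecting, as significant at the 5% level", "a between-group difference of 3.5 repetitions in the 1-minSTST (primary outcome"), "using a standard deviation of 4 repetitions" (Sample Size); 2 hospitals (Participants); 4 sites (Fidelity).

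**Assumed, because the article does not give them.** Site shares equal, or 50/25/15/10%; half the participants over 50 and half male; probability 0.8 or 1.0 of assigning the arm that reduces imbalance.

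**1. The plan's own figure.** n per arm = 2(1.96 + 0.842)² × 4² / 3.5² = 20.5, so 21 per arm and 42 in total. This matches the plan for a two-sided test. I use the stated 48 recruited below.

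**2. Two sites of 24, exactly 24:24 overall.** The chance of a 16:8 or worse split is 2 × Σ(k ≤ 8) C(24,k)·C(24,24−k) / C(48,24) = 0.042.

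**3. Four sites of 12, exactly 24:24 overall** (40,000 random permutations). Some site is 8:4 or worse in about 70% of allocations, and 9:3 or worse in about 29%.

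**4. Simulated minimisation of 48 participants** (6,000 runs per setting). Ranges cover the two assignment probabilities. Variance inflation is that of a site-adjusted treatment effect, (N/4) / Σ(n_T × n_C / n_site), against perfect balance within site.

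| Sites | Factors | Some site (n ≥ 4) 2:1 or worse | Mean variance inflation |
|---|---|---|---|
| 2 equal | age, sex | about 6% | about 2% |
| 2 equal | age, sex, site | about 0% | 0.1–0.4% |
| 4 equal | age, sex | 63–64% | about 7% |
| 4 equal | age, sex, site | 2–18% | 0.7–2% |
| 4 unequal | age, sex | 69–70% | about 7% |
| 4 unequal | age, sex, site | 13–37% | 1–3% |

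With 4 sites and no site factor, the 95th percentile of the inflation is about 19–20%. A hand check: sites at 8:4, 4:8, 6:6 and 6:6 give Σ = 2(32/12) + 2(36/12) = 11.33, and 12/11.33 = 1.06.

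**5. What this means for precision.** With SD 4 and 24 per arm, the standard error is 4√(2/24) = 1.15 repetitions. Inflation of 2% or 7% multiplies it by √1.02 = 1.01 or √1.07 = 1.03. At 21 per arm, normal-approximation power is Φ(3.5 / (4√(2/21)) − 1.96) = 80.9%. Dividing the first term by √1.02 or √1.07 gives 80.2% or 78.3%.

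**6. If site is left out of the model.** With 4 sites of 12, the arm difference in one site's share has SD 0.126. If that site's outcome differs by 3 repetitions (assumed), the added noise has SD 0.126 × 3 = 0.38. Then √(1.15² + 0.38²) = 1.21, a standard error about 5% wider. If the SD of 4 already contains spread between clinics, nothing is added.

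**7. Would the significance trigger fire?** For sites at 8:4, 4:8, 6:6 and 6:6, every expected count is 6. Chi-square = 4 × 2²/6 = 2.67 on 3 degrees of freedom, p = 0.45. Site would go unadjusted.

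**The case against.** The case for leaving the plan alone has real force.

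- **Only 2 recruiting hospitals are documented.** The high figures need 4 recruiting sites, which no section states. With 2, a 2:1 split is uncommon. This stands.
- **The harm is to precision, and it is small.** Imbalance arising by chance under randomised allocation is not bias in expectation. This stands.
- **The analysis works on change.** Stable differences in level between clinics therefore largely cancel. This stands in part: differences between sites in recovery or in usual care would not cancel.
- **A 48-person trial can reasonably limit its factors, and a site term may sit in an analysis plan that is not shown.** The first is a defensible preference. The second would repair the adjustment but not the allocation.

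A reader might infer more than the article supports:

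- **That the two counts contradict each other.** One counts hospitals whose clinics supply participants. The other appears where delivery of sessions is discussed. Both can be true, but the terms are undefined.
- **That the arms will be seriously unbalanced whatever the site count.** The figures depend on that count. Treating a 24-person site as independent coin tosses would overstate the two-site risk, because it ignores the near-equal arm totals.
- **That the arms will be unbalanced within therapist.** Treating therapists supervise only the intervention arm until the optional cross-over after week 4. Balance within therapist is therefore not possible in the randomised period, and a site factor would not create it.

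**Conclusion.** The point holds as a modest one. Recruiting site is absent from the allocation rule of a trial described as multi-site. The stated analysis does not reliably adjust for it, and the 2 hospitals and 4 sites are left unreconciled.

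The size turns on the number of recruiting sites. A split of 2:1 or worse in some site has a chance of about 4–6% with 2 equal sites and about 63–70% with 4, at a mean variance cost of about 2% and 7%. These figures rest on the assumed site sizes, age and sex mix and assignment probability. The sample size of 42 evaluable and 48 recruited is unaffected. The article does not support calling this a source of bias or a serious flaw.

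**What to change.** 1. State how many sites recruit and how many deliver telerehabilitation, and use the same terms in the Participants and Fidelity sections.
2. Add recruiting site as a third factor in the REDCap minimisation. It is known for both arms before allocation, whereas a delivery site applies to controls only if they cross over.
3. If allocation has begun, prespecify recruiting site, age and sex as covariates in the primary model, in place of adjustment triggered by baseline significance tests.

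The cost is one more factor in an algorithm already in use. Balance on age and sex becomes slightly looser, and allocation at a small site slightly more predictable, which a random element in the minimisation limits. The covariate route uses one degree of freedom for 2 sites or three for 4.

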### Statistical Analysis

Statistical analysis will be performed using IBM SPSS version 28 (IBM Corporation, Armonk, NY, USA). Intention-to-treat analysis of between-group changes at the end of the initial intervention/control period will use linear mixed effects model analysis of variance for the primary and secondary outcome measures, with adjustments for any statistically significant differences in baseline covariates between the groups. Maximum likelihood estimation through the linear mixed effects model analysis of variance will be used for missing data. Following an intention-to-treat analysis, a “per protocol” analysis will be undertaken using the same statistical methods. Post-hoc analyses will also be undertaken to establish characteristics of responders to the intervention. Analysis of the data from the cross-over group will use repeated measures analysis of variance to evaluate the within-group change due to the intervention. Data analysis at the 12-month follow-up will be exploratory. If adequate numbers in the control group do not cross-over to the intervention, a between-groups analysis will be undertaken. However, it is anticipated that the majority of participants in the control group will cross-over into the IG, in which case the analysis will evaluate the change from completion of the intervention to the 12-month timepoint. The level of significance for all outcomes will be set at an alpha of <0.05.

The semi-structured interviews will be transcribed and coded using NVivo 9 (QSR International, Melbourne, Vic., Australia). Thematic and descriptive qualitative analysis^40^ will be used to identify key themes regarding participant opinions, and perceived barriers and facilitators to participation in the telerehabilitation program. At least 3 investigators will review the coding to ensure it is insightful. Any discrepancies will be discussed by the research team and the coding revised accordingly.

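### Age and sex are minimised at allocation, but the significance-triggered covariate rule will in practice leave them out of the model; any cost is conservative and depends on how prognostic they are

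*Protocol article*

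**What the plan says.** Under Study Design, patients are randomised "with a minimization algorithm, stratifying for age" in two bands (50 or under, over 50) and for sex.

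Under Statistical Analysis, the primary and secondary outcomes share one approach: "Intention-to-treat analysis of between-group changes at the end of the initial intervention/control period will use linear mixed effects model analysis of variance". The covariate rule attached to it is "with adjustments for any statistically significant differences in baseline covariates between the groups". Neither age nor sex is named as a term in the model, and nothing else in the article brings them in.

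Under Sample Size, the calculation allows for no covariate adjustment: "A total of 42 participants will be required to have an 80% chance of detecting, as significant at the 5% level", "using a standard deviation of 4 repetitions" and a difference of 3.5 repetitions.

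**The concern.** The two provisions work against each other. The analysis rule looks for a baseline imbalance before it admits a covariate, and the allocation method removes that imbalance for the two factors chosen in advance as worth balancing. The rule therefore screens out the variables with the best design-based claim to be in the model.

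Balanced allocation makes the treatment estimate less variable when the balanced factors are prognostic. A model that omits those factors still counts the variance they explain as random error. Its standard error is then larger than the real sampling variation of the estimate, and part of the precision gained by balancing is not used. What is at stake is some efficiency and a test that runs below its nominal level, not validity.

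**Working it through.** **Inputs from the article.** Difference 3.5 repetitions, SD 4, alpha 5% (taken as two-sided; not stated), power 80%, total 42, allocation 1:1.

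**Assumptions not in the article.** R², the share of variance in the analysed outcome explained by age and sex, from 0 to 0.30. For the simulation: a 60/40 sex split, median age near 50, and a minimisation probability of 0.8 or 1.0.

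**1. The plan's own figure.** Per arm, n = 2(1.96 + 0.84)² × (4/3.5)² = 20.5, rounded up to 21, so 42 in total. This reproduces. With 21 per arm the standard error is 4√(2/21) = 1.234, the noncentrality is 3.5/1.234 = 2.835, and t-test power on 40 degrees of freedom is 79.0%.

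**2. Would the rule ever admit age or sex?** Trials of 42 patients were simulated, 4,000 per scenario. Under minimisation, binary age or sex showed a significant baseline difference in at most 0.02% of trials each, and continuous age in 0.1% to 0.4%. Without minimisation the rate was 4% to 5%. The rule as written is in effect the unadjusted analysis.

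**3. Size under perfect balance.** The true SD of the estimate is 1.234√(1 − R²), while the unadjusted model still reports about 1.234. Hence:

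- Type I error of the unadjusted test = 2[1 − Φ(1.96/√(1 − R²))].
- Unadjusted power: the estimate varies with SD 1.234√(1 − R²) but is tested against the larger reported standard error. Approximately Φ[(2.835 − 2.021)/√(1 − R²)], which gives 79.8%, 80.5% and 82.6%. Allowing for the estimated variance lowers these slightly, to the values in the table.
- Adjusted power: noncentral t with SD 4√(1 − R²).

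| R² | Type I error, unadjusted | Power, unadjusted | Power, adjusted | Gain |
|---|---|---|---|---|
| 0.05 | 4.4% | 79.6% | 81% | about 1 point |
| 0.10 | 3.9% | 80.2% | 83% | about 3 points |
| 0.25 | 2.4% | 82.2% | 89% | about 7 points |

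**4. Size under simulated minimisation, where balance is imperfect.**

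| R² | Excess of reported SE over true SD | Type I error, unadjusted | Power, rule as written | Power, prespecified |
|---|---|---|---|---|
| 0 | none | about 5% | 79–80% | 79–80% |
| 0.10 | 3–6% | 3.8–4.4% | 80–81% | 83% |
| 0.20 | 8–13% | 2.7–3.6% | 81–82% | 87–88% |
| 0.30 | 13–18% | 2.2–2.4% | 82–83% | 91% |

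The power forgone is about 2.5–3, 5–6 and 8–9 points at R² of 0.10, 0.20 and 0.30.

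**5. Does the form of the mixed model matter?** Yes. In a baseline plus week-4 model with complete data, adding age and sex as main effects left the standard error of the group-by-time term at 0.940, the same as without them. A fixed characteristic that shifts both visits equally cancels from the change. In that model the R² that counts is the share of variance in change.

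**The case against.** **The loss is not certain.** A reader might infer that the standard errors must be too large and power must be lost. The article does not support this. It gives no figure for how age or sex relate to the 1-minute sit-to-stand test or to its change. At R² = 0 nothing is lost. The article also speaks of between-group changes, and age and sex could predict the level of the test strongly yet its 4-week change hardly at all. This objection stands, and it is why the size is given as a range starting at zero.

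**The planned power is intact.** A reader might also infer that the trial is underpowered as a result, or that its estimate is biased. Neither follows. The 42 patients were computed without adjustment, the rule as written keeps power at about 79% to 83% throughout, and the departure from nominal level is in the conservative direction. Nor should adjusted power be compared with 79% at every R²: balanced allocation already returns some precision to the unadjusted test, and ignoring this would give gains of 2, 4 and 10 points instead of 1, 3 and 7.

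**The type I figures from the formula are best-case bounds.** They assume balance removes all variance due to age and sex. Age is balanced only at 50, so variation within each band stays random. This stands too, and the simulated ranges are the better guide.

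**The covariate list may sit in an unseen analysis plan.** This carries less weight. The article is not silent: it states a selection rule, and that rule conflicts with the allocation method. A later plan would have to replace it, not merely add detail.

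**Conclusion.** The point holds as a conditional efficiency issue. The stated rule will almost never admit the two minimisation factors; that part follows from the text and is confirmed by simulation. If age and sex predict the outcome as analysed, the unadjusted standard errors are conservative, with type I error between 5% and about 2%, and roughly 0 to 9 points of power are forgone for R² between 0 and 0.30. These sizes rest on the assumed R² and on the simulation settings, none of which the article supplies. The change is worth making because it costs almost nothing, but leaving the rule in place would not invalidate the trial.

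**What to change.** In Statistical Analysis, remove the significance-triggered rule. State instead that the primary and secondary models adjust for both minimisation factors (age and sex) and for the baseline value of the outcome, whatever the observed balance. State the form of the model as well:

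- with week 4 as the response, enter age, sex and the baseline value as covariates;
- with baseline and week 4 both as responses and a group-by-time contrast, enter age and sex with their time interactions, because main effects alone would leave the treatment contrast unchanged.

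The cost is a change of wording and about two of the 40 residual degrees of freedom for the two factors. Age and sex are already needed for allocation in REDCap and the baseline outcome is already measured, so no new data or patients are required. The sample size need not change.
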